Even for those neonatal networks where continued improvements in outcomes have been reported, there remains significant variation within and between networks. For example, several comparative studies have identified differences in mortality rates in neonates from separate networks, regions, or countries [20-27]. In one such study, Draper et al. reported that among 10 European regions, the overall survival rate for VPT infants varied from 74.8% to 93.2% [21]. More recently, in 2012 population data from the UKNC showed a greater than three-fold variation between regional networks in the percentage (range 4.7% to 16.6%) of infants born at <30 weeks gestation and admitted to neonatal units who died at ≤28 days of age [27]. Comparison of selected Australian and Scottish neonatal intensive care units (NICUs) detected a lower risk-adjusted mortality rate for VPT/VLBW infants in Australia compared with Scotland [28].

However, studies of a single or small group of sites are subject to selection bias, which can lead to erroneous conclusions when the results are generalized to the larger population. Furthermore, comparisons of mortality alone may be misleading as mortality may be declining at the cost of increasing morbidities. Measurement of mortality as an indicator of care is also a contentious issue as there are marked variations in practice between countries including initiation or withholding of resuscitation at earlier gestational ages [29]. Thus, this protocol for the International Network for Evaluating Outcomes of Neonates (iNeo) was developed to examine neonatal morbidities in conjunction with mortality using population-based data, and assess variations in practice that impact outcomes between and within countries.

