### Comparisons of neonatal outcomes between networks

#### Outcomes

The primary outcome for comparison between the networks will be a composite indicator of mortality or any of the four major neonatal morbidities (severe neurological injury, severe ROP, NEC, and BPD). Mortality will be defined as death due to any cause prior to discharge home. Severe neurological injury will be defined as ≥ stage 3 intraventricular hemorrhage (IVH) with ventricular dilatation according to the criteria of Papile et al. [38], or parenchymal injury (including periventricular leukomalacia) with or without IVH. Severe ROP will be defined as ≥ stage 3 according to the International Classification [39], or need for laser surgery or intraocular injections of anti-vascular endothelial growth factor agents. NEC will be defined as ≥ stage 2 according to Bell’s criteria [40] and BPD as oxygen requirement at 36 weeks post-menstrual age [41].

Secondary outcomes to be compared among iNeo member networks will include the individual morbidities of the composite outcome, as well as nosocomial infection defined as culture-proven sepsis (blood or cerebrospinal fluid positive for pathogenic organism) at >3 days or 72 hours postnatal age [42], patent ductus arteriosus requiring pharmacological treatment and/or surgical ligation, receipt of delivery room cardiopulmonary resuscitation, air leak syndrome, and resource utilization (length of stay and length of respiratory support). To account for potential differences in practices regarding discharge home and transfer to Level 2 community units, additional analyses will compare mortality by Day 28 after birth. All outcomes will be expressed as ratios with the denominator equal to all admissions to participating NICUs.

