#### Care-provision factors

Clinical practices represent the third and possibly most important set of characteristics that likely contribute to variation in outcomes. Variations in clinical practices are well known among neonatal communities [8]; however, no systematic prospective approach has determined, compared, and benchmarked variations associated with outcomes. Some of the key practice variations between centers and networks include referral practices (inborn vs. outborn) [62-64], differential use of the type of initial respiratory support [65-67], types and timings of surfactant administration [68], fluid management [69], timing of initiation of parenteral nutrition [70], use of donor milk, management of patent ductus arteriosus [71], availability and use of echocardiography, use of prophylactic interventions [72] (e.g., probiotics, high frequency oscillatory ventilation, phototherapy, and L-arginine), and the scope of involvement of parents.

Specific to each secondary outcome we will identify ‘top’ performing networks and networks with significant room for improvement. Subsequently, working groups of interested stakeholders from each network will be formed to determine methods to identify possible care provision practices related to such variations. Study methods will be similar to those described earlier, and will include annual snapshot surveys of each unit, detailed questionnaires specific to practices (e.g. parental presence, use of donor milk, diagnosis and management of hypotension, etc.), and in certain instances of outstanding success, a site visit with structured exploration of the practices in question. All methods of exploration will be conducted with directions from the iNeo Governing Board and Scientific Advisory Committee to protect privacy and confidentiality. Because individual unit information will not be disclosed to the iNeo Coordinating Centre, individual networks will be asked to identify willing members for such participation.

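### BPD and severe ROP on their own are rated over all NICU admissions, so deaths before assessment count as event-free and excess early mortality looks like better performance on these two outcomes

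*Protocol article*

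**What the plan says.** All of the following is in the protocol article.

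- **Denominator (Outcomes).** "All outcomes will be expressed as ratios with the denominator equal to all admissions to participating NICUs". No outcome is exempted.
- **Definitions (Outcomes).** The article defines "BPD as oxygen requirement at 36 weeks post-menstrual age". For the eye outcome, "Severe ROP will be defined as ≥ stage 3 according to the International Classification", or treatment by laser or intraocular injection.
- **Role of the components (Outcomes).** The primary outcome is a composite of death before discharge home or any of four morbidities, BPD and severe ROP among them. In addition, "Secondary outcomes to be compared among iNeo member networks will include the individual morbidities of the composite outcome".
- **Analysis (Comparisons between networks).** The composite, each component and the other secondary outcomes get crude rates and indirectly standardized ratios.
- **Use (Care-provision factors).** "Specific to each secondary outcome we will identify" the best performers and the networks with most to gain. Working groups then look for practices behind the differences.
- **Transfer (Outcomes).** To allow for differing discharge and Level 2 transfer practices, "additional analyses will compare mortality by Day 28 after birth". Nothing comparable is stated for BPD or ROP.

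**The concern.** BPD as defined can be observed only in an infant alive at 36 weeks post-menstrual age, and severe ROP only in one who lives long enough for the disease to be found. Under the stated denominator, an earlier death adds one to the denominator and nothing to the numerator. It is counted as if the infant had reached assessment free of disease.

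The covariates under Adjustment for variations in baseline population characteristics are baseline factors and illness-severity scores. They absorb mortality differences that case mix explains. Death after admission is a competing event, and any mortality difference left after adjustment passes straight into the BPD and ROP figures.

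At stake is the learning step of the project. A network could be held up as a model for BPD partly because more of its infants died before BPD could be diagnosed, and its practices would then be studied as candidates for adoption elsewhere. The Background itself warns that comparing mortality alone can mislead when morbidity moves the other way. Ranking morbidity alone over all admissions is the mirror image of that problem.

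**Working it through.** **1. The plan's own figures.** Yearly admissions in Table 1: 3,500 + 2,700 + 1,500 + 3,700 + 2,600 + 900 + 800 + 7,700 = 23,400. Over four years this is 93,600, of which Canada has 4 × 2,700 = 10,800 and the rest 82,800, as stated under Statistical power for outcome comparisons. A two-sided 5% test of two proportions with pooled variance at 80% power, 10,800 against 3,200, detects 0.0066 at a 1% rate and 0.028 at 40%. This matches the stated 0.007 to 0.03. Against 82,800 it detects 0.0030 and 0.014, so the stated 0.004 to 0.02 is slightly conservative.

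**2. Formula.** Let s be the BPD rate among infants alive at 36 weeks and d the share of admissions dying earlier. The rate over all admissions is s × (1 − d). For two networks with the same s, the spurious difference is s × (d2 − d1) and the spurious rate ratio is (1 − d2)/(1 − d1), which does not depend on s.

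**3. Inputs.** The documents give no s, so 30% is assumed, with 20% to 40% as the range. For d, the Background cites 4.7% to 16.6% dying by 28 days, among infants under 30 weeks in regional networks of one country. All those deaths precede 36 weeks. A milder 5% versus 10% is assumed as a second case.

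**4. Results at s = 30%.**

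| Early mortality | BPD over all admissions | Spurious difference | Rate ratio |
|---|---|---|---|
| 4.7% vs 16.6% | 0.30 × 0.953 = 28.6%; 0.30 × 0.834 = 25.0% | 0.30 × 0.119 = 3.6 points | 0.834/0.953 = 0.875 |
| 5% vs 10% | 0.30 × 0.95 = 28.5%; 0.30 × 0.90 = 27.0% | 0.30 × 0.05 = 1.5 points | 0.90/0.95 = 0.947 |

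For the wider mortality range the difference is 2.4 points at s = 20% and 4.8 at s = 40%. For 5% versus 10% it is 1.0 and 2.0 points.

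**5. Chance that the artefact is declared significant.** For 28.6% versus 25.0% with 10,800 and 3,200 admissions, the standard error is 0.00902 under the null and 0.00881 under the alternative. Power is Φ((0.0357 − 1.96 × 0.00902)/0.00881) = 98%. With Bonferroni over 8 × 7/2 = 28 pairs (critical value 3.12) it is 80%. For 28.5% versus 27.0% the standard errors are 0.00905 and 0.00897, and uncorrected power is Φ((0.0150 − 1.96 × 0.00905)/0.00897) = 38%. These are crude comparisons without covariates or clustering.

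**6. Death combined with BPD.** At s = 30% and the wider mortality range, death-or-BPD is 4.7% + 28.6% = 33.3% versus 16.6% + 25.0% = 41.6%. The high-mortality network now looks worse, the reverse of its apparent advantage on BPD alone.

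**7. Transfer (conditional).** Suppose 10% are transferred before 36 weeks, s = 25%, and later outcomes are not retrieved but coded as no event (all assumed). The recorded rate is 0.25 × 0.90 = 22.5%. The true rate is 22.5% + 0.10 × 0.25 × r, where r is the transferred infants' relative risk: 23.1% at r = 0.25 and 25.0% at r = 1. Day-28 mortality cannot correct this. It does not measure BPD, and an infant born at 28 weeks reaches 36 weeks only at day 8 × 7 = 56.

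**The case against.** **The primary outcome counts death.** The article sets out to look at morbidity together with mortality, and mortality and the composite will be reported beside BPD and ROP. This stands. A reader might infer from the one-denominator rule that high-mortality networks look better on every outcome. The documents do not support that: in the composite the effect of death runs the other way. The concern is limited to BPD and severe ROP when each is ranked alone.

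**Transfer is not settled by the text.** A reader might also infer that infants moved to Level 2 units are coded event-free, so that the composite is biased as well. The article never says so. Counting deaths up to discharge home suggests that follow-up may continue after transfer, and variable definitions are referred to an additional file not shown here. This stands, and the transfer point is made only conditionally.

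**The mortality range is extreme.** It is the lowest against the highest regional network in one country, for infants under 30 weeks, whereas iNeo compares national networks with broader eligibility. Adjustment would shrink the effect to the mortality that case mix does not explain, and Bonferroni raises the bar for pairs. All of this stands for the size of the bias. It does not remove the mechanism or its direction.

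**Survivor-only denominators are no clean cure.** They condition on a post-admission event: if the sickest infants die, the survivors are healthier and the high-mortality network may still look better. Nor should oxygen status at earlier transfer replace the stated 36-week definition. Length of stay over all admissions is a legitimate measure of resource use, so restricting it to survivors is a preference. These objections stand and shape the fix.

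**The ranking is only exploratory.** It starts working groups and is not a final inference. That lowers the stakes somewhat, but the choice of which networks to learn from is still made on these figures.

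**Conclusion.** The point holds for stand-alone BPD and severe ROP. The all-admissions rule is stated explicitly, so this is a choice to correct and not a detail left to another document. Death before assessment counts as absence of disease, baseline adjustment removes only the part that case mix explains, and 'top' networks are chosen on these outcomes.

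With an assumed 30% BPD rate among survivors, equal in both networks, the spurious gap is 3.6 points in an upper-end mortality contrast and 1.5 points in a milder assumed one. Against stated detectable differences of up to 2 to 3 points, the first exceeds them and the second is smaller but of the same order. No corresponding figure is offered for ROP, because the documents give neither a rate nor an age at examination; the direction is the same.

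Death does not flatter the primary composite. The composite and the components would both be biased by transfer if later outcomes are not retrieved and are coded as no event, which the article leaves open.

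**What to change.** 1. Keep all admissions as the denominator for mortality and the primary composite.
2. Add death-or-BPD and death-or-severe-ROP over all admissions as secondary outcomes, and name 'top' networks for these morbidities on the combined versions.
3. Report BPD among infants alive at 36 weeks, and severe ROP among infants alive at the age of assessment, only as companion figures, with a note that they condition on survival.
4. State whether BPD and ROP are retrieved after transfer to Level 2 units, and code transferred infants the same way in all networks. Where an outcome cannot be retrieved, record it as unknown and not as absent.

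The cost is a few additional derived outcomes to define and report. The combined versions need only the component indicators and deaths that the composite already requires. Retrieving outcomes after transfer, if not already done, would be the only added data work.

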#### Adjustment for variations in baseline population characteristics between networks

Demographic characteristics and severity of illness are well known to impact neonatal outcomes [43] and are also likely to vary between networks. To prevent bias, these potential confounders will be controlled in analyses comparing network-level outcome rates. The common minimum dataset includes important predictors, such as gestational age, sex, plurality of pregnancy, and receipt of antenatal corticosteroids, which will be used to adjust analyses as appropriate. In addition, most networks collect various measures of ‘severity of illness’, such as CRIB [44], SNAPPE-II [45], or TRIPS [46] scores. These will be standardized within each network (assigned a score between 0 and 1) and adjusted for in analyses.

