### Database variables

A detailed review of all the data items collected by each of the participating networks has been conducted and the elements common to all networks (e.g. gestational age, birth weight, sex, etc.) included in a minimum dataset (see Additional file 1 for full list of data variables). Data items that are collected by all networks in slightly different formats (e.g., nosocomial infection, which can be defined by using a cut-off of 2 days, 3 days, or 7 days) have been standardized across all the networks by consensus of the network directors. Some networks already extract data from their databases according to the iNeo definitions, while others have agreed to redefine their original data formats as an ongoing process to ensure consistency and facilitate comparisons over time. The variable definitions have been mapped to the ICD-10 [36] and SNOMED [37] dictionaries.

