#### Comparisons between networks

For the primary composite outcome, each of its components and the additional secondary outcomes, initial crude rates, and associated 95% and 99% confidence intervals will be calculated and graphically displayed using ‘caterpillar plots’ to visually identify differences between networks. To adjust for multiple baseline characteristics, standardized outcome ratios will be computed using the ‘indirect standardization’ approach. Each network’s observed rate will be compared with the expected rate based on the total sample from all other networks to identify networks with rates significantly above or below average. For each outcome, the expected number of events will be computed as the sum of predicted probabilities from a multivariable model (logistic regression or zero inflated negative binomial models based on data distribution) derived using data from all other networks with adjustment for confounders. Network standardized outcome ratios will be graphically displayed using ‘funnel’ plots with 95% and 99% prediction intervals for comparison between networks.

A global comparison, as well as pair-wise comparisons between networks, will be performed using multivariate regression models adjusted for confounders. Statistical models will employ generalized estimating equations to adjust analyses for clustering of infants within networks. In addition, hierarchical random-effects regression models will be used to allow for variation at the network and unit level. Statistical significance will be evaluated by applying a Bonferroni correction to account for multiple pair-wise comparisons.

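### Severity scores rescaled to 0–1 inside each network are used to adjust comparisons between networks; they can fail to control severity and can add bias

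*Protocol article*

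**What the plan says.** The Protocol article, section on adjustment for variations in baseline population characteristics, opens with the reason for adjusting: "Demographic characteristics and severity of illness are well known to impact neonatal outcomes [43] and are also likely to vary between networks". It continues: "To prevent bias, these potential confounders will be controlled in analyses comparing network-level outcome rates".

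Two kinds of covariate follow.

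- **Common items** from the minimum dataset: "gestational age, sex, plurality of pregnancy, and receipt of antenatal corticosteroids, which will be used to adjust analyses as appropriate".
- **Severity scores**, which are not common to all: "most networks collect various measures of" severity, with CRIB, SNAPPE-II and TRIPS as examples. The rule for these is "These will be standardized within each network (assigned a score between 0 and 1) and adjusted for in analyses".

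The section Comparisons between networks then uses confounder-adjusted models in two ways. Expected events for each network's standardised ratio come from a model "derived using data from all other networks with adjustment for confounders". In addition, "A global comparison, as well as pair-wise comparisons between networks, will be performed using multivariate regression models adjusted for confounders".

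The article does not give the 0–1 transform. It describes no calibration of the scores across instruments or networks, and it does not restrict the rescaled score to comparisons inside one network.

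**The concern.** A covariate controls confounding between networks only if a given value means the same severity in each of them. Rescaling inside each network works against that, because the network is the unit being compared. Depending on the transform, a network with sicker infants can end up with much the same 0–1 distribution as one with healthier infants. Indirect standardisation adds a second difficulty: the score's coefficient is estimated in the other networks, possibly on other instruments, and then applied to the index network. Networks that collect no score have nothing to enter.

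At stake is the first aim, the comparison of outcomes among networks. The section on care-provision factors goes on to identify top performers and networks with room for improvement. If severity is not controlled, case mix could be read as quality of care, under models described as severity-adjusted.

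**Working it through.** The plan states no figure to reproduce here. The check is algebra confirmed by simulation. Group sizes of 10,800 and 82,800 come from the section on statistical power for outcome comparisons. All severity distributions, slopes and gaps are assumptions. The true network effect is null throughout.

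**Step 1. What the possible transforms do.**

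- *Rank or percentile within network:* every network gets the same distribution with mean 0.5, so the between-network difference is gone.
- *Observed min-max within network:* the scale depends on each network's most extreme infants. The difference is usually distorted or partly lost. It is kept if networks share an instrument and all reach its full range.
- *Instrument's fixed range:* differences are kept among networks sharing an instrument. This is hardly standardising within a network, and equal values on CRIB, SNAPPE-II and TRIPS are not equal severity.

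**Step 2. Severity as the only covariate.** One shared 0–100 score, log-odds 0.05 per point, index network 5 or 10 points sicker. OR is the network odds ratio and SOR the indirectly standardised ratio; the null value is 1 for both.

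| Adjustment | OR, 5 / 10 points | SOR, 5 / 10 points |
|---|---|---|
| No score | 1.23 / 1.59 | 1.16 / 1.38 |
| Within-network rank | 1.25 / 1.67 | 1.16 / 1.38 |
| Within-network min-max | 1.19 / 1.48 | 1.12 / 1.27 |
| Common scale | 0.99 / 1.00 | 0.99 / 1.00 |

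The rank SORs equal the crude rate ratios: 0.2863 / 0.2466 = 1.16 and 0.3434 / 0.2481 = 1.38. Rank adjustment therefore removed nothing. Under min-max the scaled means were 0.210 against 0.200 in the 5-point case, compared with 0.249 against 0.200 on the common scale. About 0.010 / 0.049 = 20% of the gap survived.

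**Step 3. Gestational age in every model on a common scale.** Let g be gestational-age risk and s severity, both in SD units, with correlation 0.6 and log-odds 0.5 + 0.5 per SD. If s is centred within network, the network term absorbs 0.5 × (the between-network difference in mean s).

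- *Severity gap of 0.5 SD beyond gestational age:* exp(0.5 × 0.5) = exp(0.25) = 1.28.
- *Networks differing by 0.5 SD in g only:* mean s differs by 0.6 × 0.5 = 0.3, so exp(0.5 × 0.3) = exp(0.15) = 1.16.

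Two separate simulations of these scenarios, given as a range where they differ:

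| Network OR | 0.5 SD severity gap | Gestational age differs only |
|---|---|---|
| No score | 1.27–1.28 | 1.00 |
| Within-network rank | 1.28–1.29 | 1.15–1.16 |
| Within-network min-max | 1.20–1.31 | 1.18–1.20 |
| Common scale | 1.00–1.01 | not reported |

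In the last column, gestational age alone is sufficient. The rescaled score takes over part of the gestational-age coefficient but cannot carry the shift between networks, so it creates a difference that was not there.

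**The case against.** The strongest reply is that the transform is unstated and that a condensed article may leave it to the full plan. Under one natural reading the problem can vanish. With a bounded 0–100 score on one shared instrument, both networks reaching 0 and 100, and means 3, 6 or 9 points apart, the unadjusted OR was 1.15 / 1.29 / 1.46, while within-network min-max gave 1.01 / 1.00 / 1.01, the same as the raw scale. This stands. A reader might infer that the rule always removes the severity difference, or leaves all severity confounding in place. The document does not support that: it is exact for rank or percentile scaling only.

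Second, gestational age, sex, plurality and antenatal steroids stay on a common scale, so only severity beyond these is at issue. That also stands, although Step 3 shows that gestational-age adjustment does not rescue the rescaled score.

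Third, a reader might set a simulated bias, in percentage points, against the detectable differences of 0.004 to 0.03 in the power section. The document gives no between-network severity gap, so this would weigh an invented scenario against a planning figure.

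Fourth, dropping the score does not cure severity confounding. In a simulation with a gestational-age-like covariate, omission left an OR of 1.39, 1.16 or 0.99 when 0%, 50% or 100% of the severity gap ran through that covariate.

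The first objection does not dispose of the point. Rescaling inside each network is a stated choice, not an omitted detail, and the favourable case needs a shared instrument, whereas the article names three and says that only most networks collect a score.

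**Conclusion.** The point holds in this form: the severity score as specified is not a dependable adjuster for comparisons between networks. It can fail to control severity, and when networks differ in gestational age it can add bias that gestational-age adjustment alone would not have.

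Under the assumptions shown, a 0.5 SD severity gap leaves an OR of 1.20 to 1.31 with the rescaled score, against about 1.00 on a common scale. A 0.5 SD gestational-age difference produces 1.15 to 1.20 where omitting the score gives 1.00. These sizes scale with the assumed gap, slope and correlation, none of which the document supplies. For rank scaling the mechanism does not depend on the particular values. For min-max it depends on the score distribution, and the effect can be nil.

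**What to change.** 1. Keep within-network-standardised scores out of the primary between-network models: the standardised ratios and the global and pair-wise tests.
2. Adjust those models for covariates measured on a common scale: gestational age, birth weight for gestation, sex, plurality and antenatal steroids. The section on database variables and the adjustment section indicate that these are available; the former describes "the elements common to all networks (e.g. gestational age, birth weight, sex, etc.) included in a minimum dataset".
3. Use severity scores on their original scale in sensitivity analyses among networks sharing an instrument or, if feasible, after calibrating the instruments to a common risk scale.
4. Keep within-network scores for comparing units inside one network, where they do adjust for severity.

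Steps 1, 2 and 4 change only the analysis wording and need no new data; calibration in step 3 would take additional work. The price is that severity confounding beyond the common covariates remains in the all-network comparison. The plan should say so as a limitation.
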